## Abstract

**Background:**

Intervertebral disc degeneration is emphasized as an important cause of low back pain. Current surgical treatment provides relief to the accompanying pain and disability but does not restore the biological function of the intervertebral disc. NOVOCART™ Disc plus, an autologous cell compound for autologous disc chondrocyte transplantation, was developed to reduce the degenerative sequelae after lumbar disc surgery or to prophylactically avoid degeneration in adjacent discs.

**Methods/design:**

This is a multicenter, randomized, controlled, clinical phase I/II combination study. A total of 120 adult patients are allocated in a ratio of 2:1:1. Sample size and power calculations were performed to detect the minimal clinically important difference of 10 units, with an expected standard deviation of 12 in the Oswestry Disability Index, which is the primary outcome parameter. Secondary outcome parameters include the visual analog scale and the EQ-5D questionnaire. Changes in physical and mental health are evaluated using the Short Form-12 (SF-12). Moreover, radiological and functional outcomes are evaluated. The major inclusion criterion is a single lumbar disc herniation that requires sequestrectomy. Transplantation is performed 90 days thereafter. Study data generation (study sites) and data storage, processing, and statistical analysis are clearly separated.

**Discussion:**

In this phase-I/II study, NDplus is being investigated for its clinical applicability, safety, and efficacy in the repair of herniated, nucleotomized discs, and of adjacent degenerated discs, if present. To date, autologous disc chondrocytes have not been transplanted into degenerative discs without previous disc herniation. As such, this is the first study to investigate a therapeutic as well as a prophylactic approach to treat degenerative discs of the lumbar spine.

**Trial registration:**

EudraCT No: 2010-023830-22, ID NCT01640457, 8 November 2010

## Background

The vast majority of low back pain (LBP) is self-limited or successfully treated conservatively, whereas a small proportion of patients develop chronic LBP intractable to nonsurgical treatments. These patients present an increasing medical and socioeconomic problem [1]. Intervertebral disc degeneration (IVDD) is emphasized as an important cause of LBP [2, 3]. With progressive degeneration, the effectiveness of the nutrition mechanism of the intervertebral disc decreases; in consequence, the nucleus pulposus cells lose their ability to produce proteoglycan and other important extracellular matrix proteins, which results in disc desiccation and progressive instability [4]. Most treatment approaches, for example, the aggressive removal of the pathological disc or spondylodesis, do not address options of restoring structural or biological deteriorations when IVDD is the underlying problem. However, cell retransplantation and restoration, as a procedure used in this trial, would offer a less invasive and biological alternative to lumbar fusion in an attempt to obviate the LBP associated with IVDD earlier in the degenerative cascade. Until now, an intervertebral disc may only be repaired biologically after a herniation through the transplantation of the patient’s disc chondrocytes [5–8].

Results of the application of ADCT showed that cellular revitalization of the intervertebral disc is possible [8], and the results of a prospective randomized and controlled multicenter trial for ADCT were promising [9]. For the survival and the adaptation of the cultivated cells to the harsh environment in the disc space, the availability of nutrients, the number of injected cells required to avoid nutritional problems due to cell overpopulation, and the pro-inflammatory environment play a crucial role. These problems should be overcome with a suitable biomaterial, which is used in this study [10].

By using an initially liquid biomaterial, which polymerizes after being injected, the cells adhere much better to the disc tissue. NOVOCART™ Disc plus (NDplus), an autologous cell compound for autologous disc chondrocyte transplantation (ADCT), was developed to provide rehydration and maintain the biological integrity of degenerative lumbar discs to prevent secondary diseases such as recurrent lumbar disc herniation, osteochondrosis, or segmental instability. The important properties of NDplus are anti-inflammatory, antiangiogenic and antiosteogenic. Moreover, NDplus is hydrophilic, supports cell morphology, and stabilizes the chrondrogenic phenotype.

In this phase-I/II study, NDplus is being investigated for its clinical applicability, safety, and efficacy in the repair of herniated, nucleotomized discs and of adjacent degenerated discs, if present.

The objective of this clinical study is to provide the basis for a confirmatory study design (endpoints and methodologies) (phase II) and to develop a safety profile for the surgical procedure as well as for NDplus (phase I). This study further aims at developing and validating known and new biologic markers for the quality and clinical efficacy of NDisc plus as requested in the context of identity, purity, and potency characteristics of the medicinal/investigational product.

## Methods/design

### Study design

The NOVOCART™ Disc study is a nonconfirmatory, prospective, multicenter, unmasked, randomized study with two phases aimed at gathering preliminary clinical information on NOVOCART™ Disc plus and NOVOCART™ Disc basic used in the treatment of a herniated disc. Phase I aimed to develop a safety profile of the investigational medicinal product NOVOCART™ Disc plus. The objectives of phase II are mainly to provide a basis for a confirmatory clinical trial design and proof of concept. Twelve trial sites are planned to participate in this combined phase-I/II study; three of them have already participated in phase I. In total, 120 patients meeting the inclusion criteria will be randomized, treated according to the randomization, and followed up for 5 years. The primary study endpoint of the phase II is the difference in the Oswestry Disability Index (ODI) between treatment groups 2 years after the intervention. This index has emerged as the most commonly recommended condition-specific outcome measure for spinal disorders. It is a self-administered questionnaire divided into 10 sections designed to assess the limitations of various activities of daily living [11, 12]. The Short Form-36 (SF-36) questionnaire and EuroQuality of Life-5 Dimension (EQ-5D) are applied to assess changes in health status and quality of life [13, 14]. Moreover, changes in leg and back pain are assessed by the Visual Analog Scale (VAS) [15]. Numerical measurements in the disc height, volumetry, and signal intensity of index and adjacent discs and categorical evaluations, such as degeneration scale and the presence or absence of stenosis, are determined by magnetic resonance imaging (MRI). Neurological and functional status and the quantity of current pain medication and time to return to work after surgery are documented. The serology of HIV, hepatitis and *Treponema palladium* are determined preoperatively. Laboratory values (IL-6, Leukotriene, and CRP) as safety vales are being evaluated only in phase I of the study. Adverse events and serious adverse events are documented. Histological investigation of the explanted tissue is performed. Primary and secondary outcome parameters are outlined in more detail in Table 1.

**Table 1 Tab1:** Primary and secondary outcome parameters

Primary outcome parameter	Oswestry Disability Index (ODI), German and Austrian version, at 5 years’ follow-up to measure degenerative lumbar disc-related disability. [11, 12]
Secondary outcome parameter	Changes in health status and quality of life will be captured by the Short Form-36 (SF-36) version 2.0 questionnaire [14] and EuroQuality of Life 5-Dimension-3 L (EQ-5D-3 L) questionnaire [13]
	Pain relief, as defined by improvement on 100 mm visual analog scale for back and leg pain [15].
	Index level and adjacent disc on magnetic resonance imaging (MRI)
	• by evidence of disc degeneration (Pfirrmann Classification) or osteochondrosis (Modic Changes) [30–32]
	• by numerical measurements in disc high, volumetry, and signal intensity
	• by T2 relaxation
	• by the presence or absence of stenosis.
	Pain medication usage will be assessed by a four-level score (0 = none to 3 = high level of usage).
	Work status and time to return to work
	Neurological status will be evaluated using the Jenny Scale as a neurological test for the lower extremities, including motor and sensory deficits, reflexes, sciatic stretch ability and walking range.
	Functional status:
	• by posture and gait
	• by finger-ground distance
	• by Schober’s sign
	• by precision tenderness/pressure pain

### Trial organization, registration, and ethical aspects

Ethics approval was attained in Germany from the National Physician Board, “Landesärztekammer” Sachsen-Anhalt and in Austria from the committee of the Medical University Innsbruck. Furthermore, the clinical trial approval was obtained from the Paul-Ehrlich-Institute (Langen, Germany) and the Austrian Agency for Health and Food Safety (Vienna, Austria). The ethical bodies that approved the study in the various centers are listed in Table 2.

**Table 2 Tab2:** Ethical bodies of the various centers

Study site	Ethical body
Innsbruck	Committee of the Medical University Innsbruck
Speising	Committee of the Medical University Vienna
Halle	National Physician Board Sachsen-Anhalt
Murnau	National Physician Board Munich
Münster	National Physician Board Westfahlen-Lippe
Kiel	Committee of the Medical University Kiel
Karlsruhe	National Physician Board Baden-Württemberg
Berlin	National Physician Board Berlin
Göttingen	Committee of theMedical University Göttingen
Idar-Oberstein	National Physician Board Mainz
Düsseldorf	Committee of the Medical University Düsseldorf

The study complies with the World Medical Association Declaration of Helsinki Ethical Principles for Medical Research Involving Human Subjects, Good Clinical Practice (GCP), national pharmaceutical acts in the participating countries (Austria and Germany), and European guidelines for the conduct of clinical trials with medicinal products for human use. The trial is initiated and sponsored by TETEC Ag (B|Braun Aesculap AG shared company, Reutlingen, Germany), which is responsible for management and registration (EudraCT No: 2010-023830-22, ID NCT01640457). CenTrial GmbH (Tuebingen, Germany) is responsible for clinical trial submission, independent clinical monitoring, and pharmacovigilance. Mediri GmbH (Heidelberg, Germany), as a core imaging lab, is responsible for the development of the MRI protocols, data storage and analyses. Laboratory values are investigated centrally by Synlab Services GmbH (Synlab MVZ, Leinfelden-Echterdingen, Germany). Accovion GmbH (Eschborn, Germany) is responsible for data management, biometrics, and medial writing. Quality assurance is being done in cooperation with participating clinical research organizations (CRO).

### Study population

The N-Disc trial aims to include patients who qualify for lumbar sequestrectomy because of a lumbar disc herniation. The target population consists of patients with symptomatic lumbar disc herniation who failed adequate conservative or interventional treatment approaches in accordance with the guidelines of DGNC and DGOOC. Additionally, an MRI-determined lesion at treatment level needs to correlate with the primary symptoms. To minimize risk factors, patients with significant comorbidities have been excluded from the study. Written informed consent has been obtained from each patient. Inclusion and exclusion criteria are outlined in more detail in Table 3.

**Table 3 Tab3:** Inclusion and exclusion criteria

Initial inclusion criteria	A disc herniation with back and/or leg pain (radicular pain)
	Indication for sequestrectomy according to the guidelines of German Society of Neurosurgery and the German Society of Orthopedics and Orthopedic Surgery
	Age between 18 and 60 years
	Physically and mentally able to participate in the study and able to understand the study, its goals, and the possible risk factors involved
	Willing and able to participate in the follow-up visit plan at the study site and able to understand and to complete a study-relevant questionnaire in German language
	Sufficiently informed about this trial orally and in writing. She/he had enough time for consideration, is willing to participate in the study, and gives her/his written informed consent
	No participation in a clinical study 90 days prior to study inclusion. She/he agrees to refrain from participating in another clinical study during the NOVOCART™ Disc Study and for another 90 days after study termination
Initial exclusion criteria	Previous surgery at the lumbar level(s) and has been treated with NOVOCART™ Disc plus or NOVOCART™ Disc basic
	Recurrent disc herniation treated with nucleotomy/sequestrectomy of the relevant disc
	Degenerative muscular or neurological conditions that would interfere with evaluation of outcome measures, including but not limited to Parkinson’s disease, amyotropic lateral sclerosis, multiple sclerosis, muscular dystrophy, and myelopathic diseases of different causes
	Body Mass Index?>?35 kg/m2
	Current or recent history of illicit drug, nicotine (more than 20 cigarettes per day) or alcohol abuse or dependence
	CRP?>?10 mg/dl
	Pregnant, breastfeeding or planning to become pregnant. Female patients must be either at least 2 years postmenopausal or using one of the following means of birth control during the treatment phase, that is, for transplantation
	• surgical sterility
	• double barrier methods, for example, condom or diaphragm in combination with spermicide
	• intrauterine contraceptive device
	• bilateral vasectomy of sexual partner at least 90 days prior to enrollment in combination with barrier methods (for example, condom or diaphragm)
	• birth control pill
	History of known allergies or a suspicion of allergies to any of the NOVOCART™ Disc plus or basic product components, including hyaluronan, polyethylene glycol or albumin
	Immune defects or the affinity for infections of known or unknown causes
	Active systematic or local microbial infection, eczematization, or inflammable skin alterations at the site of surgery
	Unable to undergo magnetic resonance imaging
	History or suspicion of a disease with chronically inflammable character, as rheumatoid arthritis, gout, pseudo-gout, metabolic bone diseases, Crohn’s disease, ulcerative colitis, lupus erythematosus, or other autoimmune disorders
	Known osteoporosis
	Primary hyperparathyroidism or hyperthyroidism, chronic renal failure, or previous fragility fractures
	Systematic connective tissue or collagen disease
	Hereditary ocular degeneration with unclear diagnosis, retinopathies based on connective tissue-defined causes, macular corneal dystrophy
	Immune suppression
	History of blood coagulation disease of different genesis, including known hemorrhagic diathesis of unknown cause
	Chemo or radiotherapy within the past 5 years or had any cancer other than nonmelanoma skin cancer treated with curative intent within the past 5 years
	Known diabetes, drug treated
	Ulterior concomitant diseases or functional impairments of specific organs, which exclude study participation by the assessment of the investigator
Radiological inclusion criteria	Single level lumbar disc herniation
	More than 50 % remaining disc height in the herniated disc in comparison to unaffected discs in the lumbar spine. If all discs show degenerative signs, disc height must be at least 5 mm
	No obvious signs of osteophytes and no endplate sclerosis in the lumbar segment to be treated with NOVOCART™ Disc plus or NOVOCART™ Disc basic
	Patients without adjacent degenerative discs (HD): adjacent proximal disc has no degenerative signs according to Pfirrmann Score stage 3 to 5
	Patients with adjacent degenerative discs (AAD): additional degenerative signs in the proximal adjacent lumbar level according to Pfirrmann 3 to 4 but no more than 25 % disc height reduction
Radiological exclusion criteria	Degenerative changes in the lumbar spine as determined by Modic Changes 2 to 3
	One or more dysplastic vertebral bodies within the lumbar spine
	Sacralized lumbar vertebra LWK 5 at the level to be treated with NOVOCART™ Disc plus or NOVOCART™ Disc basic
	Previous or acute spondylodiscitis
	Segmental instability (spondylolisthesis?>?5 mm) or translation?>?3 mm
	Isthmic spondylolisthesis, ankylosing spondylitis, or spondylolysis
	Lumbar scoliosis (>11° deformation)
	Previous trauma, discography or any other surgical intervention at the lumbar spine
	Previous compression or burst fracture at the level(s) to be treated with NOVOCART™ Disc plus or NOVOCART™ Disc basic
	Central spinal canal stenosis with evidence of a narrowing of?<?8 mm (by sagittal MRI)
	Spinal tumor
	Metabolic bone disease
	Facet ankylosis or severe facet degeneration
	Lumbar kyphosis
Intra-surgery exclusion criteria	Extensive damage of annulus, which subsequently poses a significantly greater risk of recurrence
Exclusion criteria after sequestrectomy	HIV, *Treponema pallidum*, active hepatitis B or C infection
Exclusion criteria prior transplantation	Recurrent disc herniation after surgery and prior transplantation

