### Transplantation

Transplantation is performed 90 days after sequestrectomy. N Disc plus (NDplus) or N Disc basic (NDbasic) is applied via an injection with a dual-needle technique directly at the intended site of action. NDplus or NDbasic is to be transplanted in a comfortable lateral or abdominal position. After the treatment level is localized and local anesthesia is performed, the puncture of the intervertebral disc concerned takes place contralaterally to the disc surgery. An injection needle is placed in the center of the disc space under image guidance, and the medicinal product is injected. In case of an ADD (adjacent disc degeneration), positioning of the needles and the mandrin takes place simultaneously to minimize radiation exposure (Fig. 2).

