### Randomization

Randomization is performed intraoperatively by envelope and separately for phase I and phase II of the study. In phase I, 24 patients are randomly assigned to NDplus and NDbasic in a 1:1 allocation ratio. In phase II, 96 patients are randomly assigned to NDplus, NDbasic or follow the standard of care treatment (surgery only, SC). The allocation ratio in phase II is 2:1:1. Altogether, 60 patients will be assigned to NDplus, 36 to NDbasic, and 24 to SC (Fig. 3). Two randomization schedules are generated by CROs using Rando™ (CRO’s proprietary randomization software). The randomization schedule is kept at the CRO by the randomization code administrator, who is independent from the study team. A copy of the randomization schedule is provided to TETEC AG.

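### Re-herniation before transplantation is an exclusion that acts after randomisation and is worded around a procedure the SC arm never has; unless everyone is analysed as randomised, both contrasts with SC lean towards injection

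*Protocol article*

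**What the plan says.** All references are to the protocol article.

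- **Allocation** (Randomization): "Randomization is performed intraoperatively by envelope and separately for phase I and phase II of the study". Phase I has two injected arms only. In phase II, patients in the third arm "follow the standard of care treatment (surgery only, SC").
- **Injection** (Transplantation): "Transplantation is performed 90 days after sequestrectomy". The abstract agrees: "Transplantation is performed 90 days thereafter".
- **Late exclusion** (Study population, Table 3, last row, for exclusions before transplantation): "Recurrent disc herniation after surgery and prior transplantation". No corresponding row for SC is given.
- **Numbers** (Study design; Sample size and power calculation, Table 4): 120 patients are to be randomised, treated as randomised and followed for 5 years. Table 4 uses 60, 36 and 24, which is all 120.
- **Analysis** (Efficacy variables): efficacy is presented in a Full Analysis Set (FAS), which the article does not define, and no imputation is planned. Differences between either injected arm and SC are read as the total effect of the product, the procedure and the waiting interval.
- **Masking** (Study design): the study is unmasked.

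**The concern.** The order of events is the problem. The envelope is opened at surgery, and a patient can be excluded during the next 90 days because the disc has herniated again. Recurrent herniation is a treatment failure. The Background names it among the conditions the product should prevent, and the section on safety variables gives increased re-herniation as an example of a reason to consider stopping the trial.

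As worded, the rule needs a planned transplantation to attach to. NDplus and NDbasic patients have one and SC patients do not. If excluded patients leave the comparison, the injected arms are cleared of early failures while nothing in the article clears SC of them. Two of the three pairwise contrasts would then mix a treatment effect with a selection effect. The Efficacy variables section attributes those differences entirely to product, procedure and interval, and does not mention selection during the interval. With no imputation, a patient excluded without later ODI data adds nothing to the simple comparison of ODI at follow-up, even if nominally counted in the FAS. Because allocation is unmasked, re-herniation is also judged with the arm known.

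**Working it through.** **1. The plan's own figures.** Inputs from the sample size section and Table 4: difference 10, SD of change 14.7 (12 × √(2 × 0.75) = 14.70), n = 60, 36 and 24. Two-sided 5% is taken from the 95% confidence intervals, since no test level is stated. Half-width = 1.96 × 14.7 × √(1/n₁ + 1/n₂). Power is from the noncentral t distribution with noncentrality 10 / (14.7 × √(1/n₁ + 1/n₂)).

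| Contrast | Half-width | Table 4 | Power | Table 4 |
|---|---|---|---|---|
| NDbasic–SC (36 v 24) | 7.59 | 7.59 | 71.9% | 71% |
| NDplus–SC (60 v 24) | 6.96 | 6.96 | 79.5% | 79% |
| NDplus–NDbasic (60 v 36) | 6.07 | 6.07 | 89.1% | 89% |

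Table 4 reproduces with all 120 patients, so it makes no allowance for anyone excluded after allocation.

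**2. Loss of power if the injected arms shrink.** Removing an assumed 5% (3 of 60; 1.8 of 36) gives 70.9%, 78.9% and 87.5% in the same order. Removing 10% gives 69.9%, 78.2% and 85.7%. The loss is small, so power is not the issue.

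**3. Bias if early failures leave the injected arms and remain in SC.** Let p be the share re-herniating before day 90 and d their excess ODI at the endpoint. With no true effect, the cleared arm has mean μ and SC has mean (1 − p)μ + p(μ + d) = μ + pd. The shift in favour of injection is therefore p × d. The article gives neither p nor d. **Both are assumptions**: p = 2–10%, d = 10–30 points.

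The type I error uses a normal approximation. The SC variance is widened for the mixture: v = 14.7² + p(1 − p)d². The standard error is SE = √(14.7² / (n(1 − p)) + v/24), with n = 60 or 36. The error is P(|Z + pd/SE| > 1.96).

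| p, d (assumed) | Shift pd | SE, NDplus–SC | Type I, NDplus–SC | Type I, NDbasic–SC |
|---|---|---|---|---|
| 2%, 10 | 0.2 | 3.57 | 5.0% | 5.0% |
| 5%, 20 | 1.0 | 3.69 | 5.8% | 5.7% |
| 10%, 30 | 3.0 | 4.05 | 11.5% | 10.6% |

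Middle row for NDplus–SC: v = 216.09 + 0.0475 × 400 = 235.09; SE = √(216.09/57 + 235.09/24) = 3.69; pd/SE = 0.27.

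**4. When the shift vanishes.** If all randomised patients are followed and analysed by arm, every arm has mean μ + pd when there is no effect, and the contrast is 0. If the same day-90 rule is applied to SC, every arm has mean μ, and the contrast is again 0.

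**5. NDplus versus NDbasic.** Both arms face the same rule before anything is injected, so p × d cancels. What remains is only the chance that unmasked judgement differs between the two.

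**The case against.** The strongest reply is that the article never says what the bias requires. Table 3 is one eligibility list for the whole trial. It uses product or transplantation wording elsewhere for criteria that apply to everyone, such as contraception and the level to be treated. The last row could therefore mark day 90 for all arms. The visit plan and the randomisation figure are not shown. An article may leave the FAS definition to the full protocol or analysis plan; if the FAS is as randomised and follow-up continues, exclusion means only that no injection is given, and the shift is zero. The study is also declared nonconfirmatory and focused on estimation.

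Much of this stands, and it limits what can be claimed. A reader might infer three stronger things that the documents do not support:

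- **That early failures stay in SC and the rule can reach only the injected arms.** This is an inference from the wording; the article neither says it nor rules it out.
- **That early re-herniations drop out of the safety count.** No passage says so. Adverse events are documented and re-herniation is monitored by MRI.
- **That the serology and annulus exclusions add to the imbalance.** The infection row stands under "Exclusion criteria after sequestrectomy", while Study design says the tests "are determined preoperatively". A preoperative test whose result is acted on later is compatible with both, and the row is not tied to transplantation, so it can apply to all arms. For annulus damage, no order relative to opening the envelope is given. Neither creates a difference between arms.

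The objection does not remove the stated rule: an outcome-related exclusion placed after allocation, tied to an event one arm lacks, beside statements that all 120 are followed and counted.

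**Conclusion.** The point holds in conditional form. The article places an outcome-related exclusion after intraoperative randomisation, words it around transplantation and gives no SC counterpart. This does not fit its own statements that 120 patients are followed for 5 years and enter the power table. If the rule takes patients out of follow-up or analysis in the injected arms only, NDplus–SC and NDbasic–SC are biased towards injection.

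The size cannot be found from the article. The 0.2–3 ODI points are 2–30% of the 10-unit target. They rest on the assumed rates and on the deficit persisting to the endpoint. At 5% and 20 points the shift is 1 point against a half-width of 6.96, which is modest; only the extreme corner raises the type I error markedly. The direction, however, is fixed whenever early failures have worse ODI, and a larger sample would not remove it. It should be settled before the 24-month evaluation, which Table 5 names as the primary one for efficacy.

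**What to change.** 1. State that patients not transplanted because of re-herniation remain in ODI follow-up and in the FAS under their randomised arm. The clinical decision about injection is left untouched.
2. Tabulate re-herniations from sequestrectomy onwards by randomised arm, so that events before and after day 90 are visible in all three arms.
3. Add a supporting analysis with one day-90 landmark applied identically to NDplus, NDbasic and SC, so that SC patients with re-herniation by then also leave it.
4. Reconcile the last row of Table 3 with Study design, Randomization, Table 4 and Efficacy variables, and say whether that row means exclusion from the study or only from injection.

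The cost is wording in the protocol and analysis plan, follow-up of a few untransplanted patients (about 3 of 60 and 2 of 36 at an assumed 5%), and a slight dilution of the estimated effect, because those patients count in an arm whose treatment they did not receive.
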